### 9.2 Analysis Variables

See section 2.1 and 2.2 for the variables to be analysed as well as section 6.8.

Cognitive impairment will be defined as cognitive scale score <70 and autistic spectrum disorders will be defined as ADOS>12.

A treatment-emergent adverse event is an adverse event that emerges after randomization having been absent pre-randomization, or worsens relative to the pre-randomization state.

### 9.3 General Considerations

All patient data entered into the eCRF will be listed. Free text will be listed only.

**Patient disposition** will be analysed based on the CONSORT statement, including number patients screened, patients randomized, patients terminating the study prematurely and the number of patients in the analysis populations.

**Screening and disease characteristics** will be analyzed descriptively by treatment group for the SAF using standard summary measures, i.e., number of evaluable observations, arithmetic mean, standard deviation, median, 25 %- and 75 %-quantile, minimum and maximum for continuous data and the number and percentage of patients per category for categorical data.

A statistical analysis plan will be written for the main study by the KKS.

All analyses of the main study will be described in the statistical analysis plan in greater detail. Additional analyses may be added. The accompanying research will not be part of this plan.

In case of any changes to the primary analysis described in this protocol an amendment will be issued pointing out the changes. If necessary, all other changes will be mentioned in the SAP, only.

SAS Version 9.4 or higher will be used for analyses.

### 9.4 Primary Analysis

As **primary analysis**, the BSID-III cognitive scale of 2 years will be analysed using a two-sided Mann-Whitney-U-test ( $\alpha=0.05$ ) stratified by age groups (0-<2 and 2-<4 months of age) comparing the treatment versus the control group. The Mann-Whitney-U-test is used instead of the t-test because there are hints that the values could be not normally distributed in this

|                                                                    |                                              |                                |
|--------------------------------------------------------------------|----------------------------------------------|--------------------------------|
| Clinical Trial Code: PROTECT
EU trial number: 2022-502332-39-00 | Trial Protocol
(Version 06; (01.10.2024)) | Page 92 of 110
CONFIDENTIAL |
|--------------------------------------------------------------------|----------------------------------------------|--------------------------------|

population. All patients randomized will be evaluated following the treatment policy strategy (ICH E9 R1).

Missing values of patients (including missing values due to early termination of the study) without a BSID-III cognitive scale at the age of 2 years will be replaced

- a) with randomly selected values of patients in the control group (single imputation) if the 1-year value is not available
- b) with data of the control patients using a linear regression model with the 1-year value as independent variable and the 2-year value as the dependent variable (single imputation) if the 1-year value is available

Values of the control group will be used in order to achieve a conservative estimate. No fixed value is used for single imputation (e.g. the median) to reduce the risk to underestimate the variance. The seed to select values randomly is 4421360.

Additionally, the median of the BSID-III cognitive scale and the corresponding 95% CI will be displayed by group.

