# 1. INTRODUCTION AND RATIONALE

## 1.1 Scientific Background

Tuberous sclerosis complex (TSC) is an autosomal dominant neurodevelopmental disorder affecting 1:6,760 – 1:13,520 live births in Germany [2] with an estimated prevalence of 1:20,000 individuals equally distributed among ethnic groups and both sexes. Penetrance and expressivity are variable ranging from mild skin lesions and minimal neurologic signs to severe neurodevelopmental manifestations, including refractive epilepsy, autism spectrum disorder (ASD) and profound intellectual disability (ID) [3, 4]. Mortality is significantly elevated, up to fivefold compared to the general population. The most common causes of TSC-attributable deaths are status epilepticus, sudden unexpected death in epilepsy (SUDEP), kidney complications, and infections. Mortality is especially increased in individuals with ID [5]. About 90% of TSC patients develop neurologic complications, such as epilepsy, ID and ASD [3, 6]. Epilepsy, usually starting during the first year of life, occurs in 83.5% of patients and is the most prevalent and challenging manifestation [3, 7]. Early-onset epilepsy typically presents with focal seizures and infantile spasms (IS). IS or West syndrome is a severe epileptic encephalopathy characterized by epileptic spasms and a pathognomonic EEG pattern (hypsarrhythmia), occurring in 38.8% of affected individuals [7]. Infantile onset epilepsy and in particular IS are suspected to cause alterations in brain maturation with significant impact on neurodevelopment and are considered the most important risk factors for neuropsychologic impairment (ID and ASD) [8]. On the molecular level, TSC is caused by heterozygous loss-of-function variants in the genes *TSC1* and *TSC2*, encoding the Tuberin-Hamartin complex, acting as a critical upstream suppressor of the mammalian target of rapamycin (mTOR), a key signaling pathway controlling cellular growth and metabolism. Haploinsufficiency of *TSC1* or *TSC2* leads to a constitutive activation of the mTOR pathway, resulting in fundamental alterations in neuronal network properties and an imbalance in neuronal excitation and inhibition, acting as a common pathway toward epilepsy, ID and ASD [9, 10]. Therapeutic mTOR inhibition is a promising molecular target for the treatment of TSC-associated manifestations. The mTOR inhibitors sirolimus and everolimus have been increasingly used in TSC and have gained approval for the treatment of TSC-related manifestations, such as subependymal giant cell astrocytomas (SEGA), renal angiomyolipomas and recently, refractory focal epilepsy above the age of 2 years. With respect to neuropsychological manifestation, preliminary trials with mTOR inhibitors in TSC children above 2 years have so far failed to demonstrate beneficial effects. This might be due to the fact that the window of opportunity for the neuromodulatory effects of mTOR inhibitors lies within the first year of life before TSC-related early-onset epilepsy and in particular IS occur as sign of disrupted brain maturation and synaptic formation. Since the influence of mTOR inhibitors on the emerging neuronal network disorder is not fully understood, the exact time at which a therapy has to be started cannot be clearly delineated. Considering the underlying molecular pathomechanisms of TSC and the fact that mTOR inhibitors can reverse many TSC-related manifestations in cell and animal models as well as in anecdotal reports [11-13], it can be hypothesized that pre-emptive initiation of mTOR inhibitor treatment reduces the risk for TSC-related neuropsychologic deficits. To date, there are no published controlled, prospective clinical trials evaluating the effect of pre-symptomatic mTOR inhibitor therapy on neuropsychologic manifestations in TSC patients under 2 years of age.

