## 9. Statistical Procedures

### 9.1 Definition of Clinical Trial Population to be Analyzed

The **safety analysis set** (SAF) comprises all randomized patients and is identical with the **full analysis set** (FAS). The **per-protocol set** (PPS) comprises all patients of the FAS who followed treatment for at least 9 months and completed neuropsychologic testing (BSID-III) at 2 years. All patients of the PPS need to fulfil the inclusion criteria 1 and exclusion criteria 1 and 2. For efficacy analyses the patients will be analysed as allocated, for safety analyses as treated.

For the analyses “as treated”, participants randomized to the Sirolimus arm are regarded as treated according to standard of care only, if

- They are lost to follow-up before 6 months after randomization or
- They never started treatment

Participants randomized to the standard of care arm are regarded as treated with Sirolimus, if

- They received prophylactic mTOR inhibitor

Screening and disease characteristics will be analysed once by treatment groups as treated.

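### Section 9.4 gives a child who is untestable because of impairment a control-derived 24-month score, which moves a bottom-ranked outcome towards the middle and is not reliably conservative

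*Protocol*

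**What the plan says.** The primary endpoint is the BSID-III cognitive scale at 24 months. Under section 9.4 it "will be analysed using a two-sided Mann-Whitney-U-test ( $\alpha=0.05$ ) stratified by age groups (0-<2 and 2-<4 months of age").

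The same section replaces the value of every randomized patient "without a BSID-III cognitive scale at the age of 2 years will be replaced". There are two branches:

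- **Branch a:** "with randomly selected values of patients in the control group (single imputation) if the 1-year value is not available".
- **Branch b,** if a 1-year score exists: a control-arm model "using a linear regression model with the 1-year value as independent variable and the 2-year value as the dependent variable (single imputation").

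The stated reason is: "Values of the control group will be used in order to achieve a conservative estimate". Neither branch depends on why the score is absent.

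The per-protocol set in section 9.1 requires that a patient "followed treatment for at least 9 months and completed neuropsychologic testing (BSID-III) at 2 years". The second sensitivity analysis in section 9.7, a linear mixed model, fills missing scores by multiple imputation from age group and the 1-year value.

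Section 6.8 describes the BSID-III with starting points and with reversal and exit rules. It does not say what is recorded for a child who cannot be tested. Section 9.3 requires a protocol amendment for any change to the primary analysis, so the replacement rule is fixed here and not left to the SAP.

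**The concern.** The protocol describes a disease spectrum "including refractive epilepsy, autism spectrum disorder (ASD) and profound intellectual disability (ID"). In such a population, a child may attend V12 and still produce no cognitive score because of the impairment itself. The absence of a score is then informative: it points to the bottom of the scale. The rule treats this child like one whose family moved away and assigns a value learned from controls who could be tested.

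The direction of the error depends on the arm. If more controls are untestable, raising them hides a benefit and costs power. If more sirolimus children are untestable, raising them favours sirolimus, the opposite of what the protocol intends by using control values. Neither sensitivity analysis corrects this, because one leaves the child out and the other imputes again without using the reason.

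**Working it through.** **Inputs from the protocol.** 30 per arm, two-sided Mann-Whitney test at 0.05, example means 75 and 90, SD 15 with alternatives 20 and 25, and 10% missing (section 9.9 and Table 8). BSID-III is scheduled at V8 (12 months) and V12 (24 months).

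**Assumptions not in the protocol.** Which children are untestable (true score below 50, or the three lowest in an arm), and the correlation between 1-year and 2-year scores (0.3 to 0.8). The simulations use the unstratified test. Repeated runs agree to about 1-2 points.

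**1. Table 8 reproduces.** With Mann-Whitney efficiency 3/π, the effective n is 30 × 3/π = 28.65 per arm, and power = Φ(Δ / (SD × √(2/28.65)) − 1.96), where √(2/28.65) = 0.264.

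| Δ | SD | Formula | Simulation | Table 8 |
|---|---|---|---|---|
| 15 | 15 | Φ(3.785 − 1.96) = 96.6% | 95.9% | >95% |
| 15 | 20 | Φ(2.839 − 1.96) = 81.0% | 79.2% | >80% |
| 15 | 25 | Φ(2.271 − 1.96) = 62.2% | 60.7% | >62% |
| 11.5 | 15 | Φ(2.902 − 1.96) = 82.7% | 81.2% | >80% |

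Replacing a random 3 of 30 per arm by branch a gives 91.1, 69.9, 51.4 and 71.5%, against the table's >90, >70, >50 and >70%. The table is thus consistent with missingness unrelated to the score.

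**2. What the rule does to the lowest children.** Take controls with mean 75 and SD 15, and let the three lowest of 30 be untestable. Their mean true score is about 50.

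- Branch a gives them the mean of the other 27: (30 × 75 − 3 × 50)/27 = 77.8.
- Branch b gives about 76, 70 or 62 at correlations 0.3, 0.6 or 0.8.
- The share of controls below 70, the protocol's threshold for cognitive impairment, falls from 37% to 30% (a) or 28-35% (b).

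**3. Power if true scores below 50 are untestable.** The expected share is Φ((50 − mean)/SD).

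| SD | Untestable, control / sirolimus | Children of 30 | Plan, branch a | Plan, branch b | Lowest rank |
|---|---|---|---|---|---|
| 15 | 4.8% / 0.4% | 1.4 / 0.1 | about 94% | 95-96% | 95-97% |
| 20 | 10.6% / 2.3% | 3.2 / 0.7 | about 68% | 72-78% | 78-80% |
| 25 | 15.9% / 5.5% | 4.8 / 1.6 | about 42% | 48-57% | 59-60% |

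Branch b is shown over correlations 0.3 to 0.8. A smaller run at SD 20 and correlation 0.4 gave 70% against 77%. Over both arms the untestable share is (10.6 + 2.3)/2, or about 6%, at SD 20 and (15.9 + 5.5)/2 = 10.7% at SD 25, so these scenarios are close to the 10% missing that the protocol assumes.

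**4. Error in favour of sirolimus.** Assume no true effect, SD 15, and the three lowest sirolimus children untestable.

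- Branch a moves them from about 50 to 75, which shifts the arm mean by 3 × 25/30 = 2.5 points in favour of sirolimus.
- Branch b at correlation 0.6 moves them to about 66, a shift of 3 × 16/30 = 1.6 points.
- False positives favouring sirolimus rise from about 2.5% to 8.0% (a) or 5.4% (b).
- With three untestable in each arm, two-sided type I error is 7.0-8.2% under the plan, against 3.6-3.8% with lowest rank.

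**The case against.** The strongest objection is that the premise is assumed. Nothing in the protocol says that severe impairment leaves a child without a score. Tasks ordered by difficulty, with reversal and exit rules, may give many impaired children a low score, which the rank test then uses correctly. This stands, and it makes the size conditional.

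A reader might infer that the worst outcomes simply leave the primary test. The documents do not support that. BSID-III is scheduled for every child at 12 months, so most children followed to V12 fall under branch b, where their own earlier score counts. At SD 20 and correlation 0.8 the loss is then only about 1 point. The branch a losses of 12 points (SD 20) and 17 points (SD 25) require that every untestable child also lacks a 1-year score.

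A reader might also take the 46% in section 1.2 as a measure of untestability. It counts a developmental quotient below 70 or autism spectrum disorder, so it includes children who had a test result.

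Nor would harm be invisible. VABS-3 and TAND rest on caregivers' reports, and the 1-year BSID-III is analysed like the primary endpoint. Section 10.1 already asks for an explanation of missing data, but no planned analysis uses it.

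Finally, lowest rank is itself a choice, and it misleads if applied to the wrong children. If three sirolimus children with ordinary true scores were ranked lowest, power at a true difference of 15 and SD 15 would be about 75%, against 92% under the planned replacement. The rule must therefore be confined to impairment and rest on a blinded judgement.

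**Conclusion.** The point holds in a conditional form. Section 9.4 fixes a replacement that ignores the reason for missingness, and for a child untestable because of impairment it raises a low outcome towards the middle. At the protocol's lead SD of 15 the cost in power is at most about 2 points. At SD 20 and 25 it is material if 1-year scores are absent (about 12 and 17 points) and ranges from about 1 to 12 points when they are present, depending on the correlation and the SD.

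The more important result is that the rule does not earn the label conservative: one-sided error in favour of sirolimus can reach about 8% (a) or 5% (b) instead of 2.5%. All of this rests on assumed numbers of untestable children and an assumed 1-year to 2-year correlation, neither of which the documents give. It should be corrected, but it does not invalidate the design.

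**What to change.** Amend section 9.4 and its dependants as follows:

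- A child seen at V12 whom the blinded examiner records as not testable because of impairment receives the lowest rank, below all observed scores, in the stratified rank test.
- The control-based replacement applies only to scores missing for other reasons.
- In section 9.1, such a child is not excluded from the per-protocol set for lack of a completed test.
- A coded field in the eCRF gives the reason for not testing, completed from the blinded examiner's record.
- The replacement as now planned, applied to all missing scores, is shown as a sensitivity analysis, because the primary result would otherwise depend on the examiner's judgement of the reason.

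The cost is one eCRF field, a few sentences in sections 9.1, 9.4 and 9.7, and the amendment that section 9.3 requires. No visit, assessor or patient is added, since section 5.1.2 already provides a blinded external examiner. The change should be made before any comparison of scores by arm.

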#### 5.1.2 Blinding

Blinding of trial personnel as well as patients is not feasible due to the nature of the interventions.

However, neuropsychologic testing will be performed by a blinded external observer (by the UKHD). The tests will be performed and the questionnaires will be scored by a person not involved in the treatment at the site of investigation. He or she has no access to any information concerning treatment of the study participant. During neuropsychologic testing no other study related activities (e.g. blood sampling) will be performed. Caregivers will be instructed not to disclose their study group. Questions from caregivers concerning the study are not discussed with the observer.

EEG recordings will be sent to the coordinating investigator and be analyzed by two independent blinded raters. The raters are not involved in the care of the participants they are evaluating and have no knowledge of their treatment status.

cMRI recordings will be sent to the coordinating investigator and be analyzed by blinded raters. The raters are not involved in the care of the participants they are evaluating and have no knowledge of their treatment status.

Abdominal sonography recordings will be sent to the coordinating investigator and be analyzed by blinded raters. The raters are not involved in the care of the participants they are evaluating and have no knowledge of their treatment status.

|                                                                    |                                              |                                |
|--------------------------------------------------------------------|----------------------------------------------|--------------------------------|
| Clinical Trial Code: PROTECT
EU trial number: 2022-502332-39-00 | Trial Protocol
(Version 06; (01.10.2024)) | Page 46 of 110
CONFIDENTIAL |
|--------------------------------------------------------------------|----------------------------------------------|--------------------------------|

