## 9.9 Sample Size/Power Calculation

It seems feasible that 60 patients can be randomized. To randomize 60 patients, 120 patients need to be assessed for eligibility assuming 50% willingness to participate in the trial. Assuming that 30 patients per group can be randomized, a difference of 15 in the cognitive scale of BSID-III at age 2 years will be detectable with a power of >95% using a two-sided Mann-Whitney-U-test ( $\alpha=0.05$  and under normality assumption with a standard deviation (SD) in each group of 15). We consider an improvement of 15 in the cognitive scale of BSID-III at the age of two years (e.g. a score of 75 in the control group and a score of 90 in the treatment group) relevant for reducing neuropsychological impairment, therefore lifting burden of disease and improving social participation and opportunities in school and professional life. The following Table 8 shows the resulting power for 30 patients per group under different assumptions:

Table 8: Power for 30 patients per group under different assumptions

| mean difference | SD per group | power | mean difference considering missing values | SD per group considering missing values | power considering missing values |
|-----------------|--------------|-------|--------------------------------------------|-----------------------------------------|----------------------------------|
| 15              | 15 (a)       | >95%  | ~ 13.5                                     | ~14.7/~15.5                             | >90%                             |
| 15              | 20           | >80%  | ~ 13.5                                     | ~19.7/~20.2                             | >70%                             |
| 15              | 25 (b)       | >62%  | ~ 13.5                                     | ~24.6/~25.1                             | >50%                             |
| 11.5            | 15 (a)       | >80%  | ~ 10.4                                     | ~14.7/~15.2                             | >70%                             |

a) [15, 99] b) [100]

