If the improvement is only 11.5 and assuming a SD in each group of 15 (sample size of 30 per group), the power is still >80%. If the mean difference is 15 and the SD is 25 in each group, the power is reduced to >62%. If the improvement is 11.5 and the SD is 25 in each group, the probability to observe an improvement (difference in medians) >5 is still >75%. An observed improvement (point estimate) of 5 still seems encouraging to proceed, as in this range it can trigger

|                                                                    |                                              |                                |
|--------------------------------------------------------------------|----------------------------------------------|--------------------------------|
| Clinical Trial Code: PROTECT
EU trial number: 2022-502332-39-00 | Trial Protocol
(Version 06; (01.10.2024)) | Page 94 of 110
CONFIDENTIAL |
|--------------------------------------------------------------------|----------------------------------------------|--------------------------------|

an individual change from mild intellectual disability to learning disability with implications on social integration, education and professional perspectives.

A rate of missing values of 10% is assumed, in accordance with assumptions made by a comparable trial of mTOR inhibitors in children with TSC [42]. In addition, the EXIST-3 trial, enrolling 366 children and adults with TSC, reported a drop-out rate of 5% [23]. Therefore, a rate of missing values of 10% seems reasonable. The table above (Table 8) shows the reduction of the power, the reduction of the effect and the change of the standard deviation considering 10% missing values and the replacement method. The standard deviation in the control group was slightly reduced, in the treatment group slightly increased on average in the simulations.

Patients with missing values (including missing values due to early termination of the study) will not be excluded from the FAS and the SAF. Therefore, patients won't be replaced.

|                                                                    |                                              |                                |
|--------------------------------------------------------------------|----------------------------------------------|--------------------------------|

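### Filling missing control scores once from other controls understates the variance of the primary test, so type I error exceeds 5% if more control than sirolimus children are lost

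*Protocol*

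**What the plan says.** Under Protocol 9.4 the 2-year cognitive scale "will be analysed using a two-sided Mann-Whitney-U-test" at a two-sided 5% level, "stratified by age groups (0-<2 and 2-<4 months of age) comparing the treatment versus the control group". A child without a 2-year score receives one replacement value. Rule a) fills the gap "with randomly selected values of patients in the control group (single imputation) if the 1-year value is not available". Rule b) uses a regression of the 2-year on the 1-year score, fitted in controls, where the 1-year score exists. Neither rule is limited to the sirolimus arm. The reason given is "Values of the control group will be used in order to achieve a conservative estimate", and the next sentence adds that drawing at random, rather than inserting a fixed value, lowers the risk of understating the variance.

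Section 9.9 keeps these children in the full analysis set. It states "A rate of missing values of 10% is assumed" without saying how losses divide between the arms. Section 9.7 uses multiple imputation, but only in a sensitivity mixed model.

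**The concern.** A control gap filled from other controls brings the control arm back to 30 scores without bringing back any information. The rank test takes its variance from 30 against 30, while the control side is known only as well as the observed controls allow. Drawing at random preserves the spread of the scores; it does not correct the overstated sample size.

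For sirolimus gaps the same understatement is more than offset, because control values pull the two arms together. Control gaps have no such offset. The error rate of the only confirmatory test therefore depends on which arm loses children, although the text describes the rule as conservative without qualification.

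**Working it through.** **Inputs.** 30 per arm, two-sided 5%, two age strata, rules a) and b) (9.4, 9.9). Differences 15 and 11.5, SD 15 to 25, 10% missing (9.9). Assumed, because the protocol does not give them: 15 children per arm per stratum, losses completely at random, and a 1-year/2-year correlation of 0.6 (range 0.3-0.8) for rule b). Loss patterns are written sirolimus/control.

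**Step 1: reproduce Table 8.** Power = Φ(d/(s·√(2/n′)) − 1.96), with n′ = 30·3/π = 28.65 for the rank test.
- 15/15: Φ(1.825) = 96.6% (stated >95%)
- 15/20: Φ(0.879) = 81.0% (stated >80%)
- 15/25: Φ(0.311) = 62.2% (stated >62%)
- 11.5/15: Φ(0.942) = 82.7% (stated >80%)

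With three of 30 missing in each arm and rule a), the expected difference is 15·27/30 = 13.5, or 11.5·27/30 = 10.35. Simulated power is 90.9%, 69.5%, 50.6% and 71.2%, against stated >90%, >70%, >50% and >70%. Table 8 therefore fits 10% missing in each arm.

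**Step 2: variance under rule a), no drug effect.** Let m_T and m_C be the losses, n = 30, n_T = n − m_T, n_C = n − m_C. Given the observed scores, the filled arms differ on average by (n_T/n) times the observed difference in means. In units of the squared SD, the true variance of the filled difference is approximately

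V = (n_T/n)²·(1/n_T + 1/n_C) + (m_T + m_C)/n².

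The test assumes 2/n = 0.0667. With R = V/(2/n), the actual type I error is 2·[1 − Φ(1.96/√R)].
- 3/3: V = 0.81·(2/27) + 6/900 = 0.0667; R = 1.00; 5.0%
- 0/3: V = 1/30 + 1/27 + 3/900 = 0.0737; R = 1.106; 6.2%
- 0/6: V = 1/30 + 1/24 + 6/900 = 0.0817; R = 1.225; 7.7%
- 6/0: V = 0.64·(1/24 + 1/30) + 6/900 = 0.0547; R = 0.82; 3.0%

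This is an approximation for a difference in means. Step 3 checks it on the rank test itself.

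**Step 3: simulation of the stratified rank test** (60,000 runs, no effect, correlation 0.6). Rule b) is run without and with a residual term.

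| Losses | Rule a) | Rule b) | Rule b) with residual |
|---|---|---|---|
| 0/0 | 5.0% | 5.1% | 5.2% |
| 3/3 | 5.0% | 5.0% | 5.0% |
| 2/4 | 5.8% | 5.7% | 5.6% |
| 1/5 | 6.6% | 6.2% | 6.1% |
| 0/3 | 6.2% | 6.1% | 5.8% |
| 0/6 | 7.8% | 7.0% | 6.7% |
| 6/0 | 3.0% | 3.6% | 3.9% |

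Over correlations 0.3-0.8, and with scores also rounded to 5 points, the range is 5.5-6.5% at 0/3 and 6.1-8.4% at 0/6. A separate, independent run of rule a) at 0/3 gave 6.8%.

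**Step 4: direction.** About half of the rejections favour sirolimus. Against a nominal 2.5%, rule a) gives 3.1% at 0/3 and 3.9% at 0/6.

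**Step 5: effect retained, true difference 15, rule a).** The expected difference is 15·n_T/30. At 6/0 this is 15·24/30 = 12.0 (simulated 12.0); at 3/3 it is 13.5 (simulated 13.4); at 0/6 it is 15 (simulated 15.0). Control losses cause no shrinkage.

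**The case against.** The strongest reply is that the plan's own loss pattern shows no fault. At 10% missing in each arm the test holds 5%, and it still holds about 4.9% when losses occur at random at that rate. Given six losses at equal rates, a 0/6 split has probability C(30,6)/C(60,6) = 1.2%, and 0/6 or 1/5 together 9.7%. This stands. The larger figures need loss rates that truly differ: with 5% sirolimus and 15% control losses, rule a) gives 6.1%; reversed, 4.0%.

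A reader might infer that control families will leave more often because the trial is open. Section 5.1.2 says only "Blinding of trial personnel as well as patients is not feasible due to the nature of the interventions", which is not evidence about dropout. The protocol also gives reasons for sirolimus losses: 13 blood samplings against 4 (1.3.4), and withdrawal for continued dosing non-compliance (5.5.5). Control families may refuse laboratory tests and stay in (6.5). The direction is unknown.

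A reader might also infer that the estimate is biased towards sirolimus. It is not when losses are at random: the mean difference is unchanged or shrunk. The word conservative in 9.4 is attached to the estimate, and in that sense it is defensible. What fails is its extension to the test, and the variance safeguard in the following sentence, which is incomplete.

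The multiple imputation in 9.7 could expose fragility but leaves the primary p-value as it is. Asking families who withdraw to attend the 24-month visit (7.3.1) limits missing scores without settling which arm they fall in.

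**Conclusion.** The point holds as a conditional defect. If more control than sirolimus children lack a 2-year score, two-sided type I error rises above 5%: about 5.5-6.8% at 0/3 and about 6-8% at 0/6, with about half of it in favour of sirolimus (roughly 2.7-4.1% against 2.5% across the scenarios run). With equal losses it stays near 5%, and with only sirolimus losses it is 3-4%. These figures rest on losses at random, normal scores (also checked with rounding), equal strata and an assumed correlation of 0.3-0.8.

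It would go too far to say that the planned test is generally anti-conservative, or that the whole excess amounts to false efficacy claims. The documents support neither. The weakness is worth correcting because the protocol fixes the rule for its single confirmatory test, nothing elsewhere corrects that p-value, and the repair is small.

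**What to change.** In 9.4, replace the single imputation by multiple imputation with pooled inference for the stratified rank test. Keep control-based imputation for the sirolimus arm, and use the 1-year score where it exists. All randomised children then stay in the analysis and imputed values are counted as imputed. Limit the statement about conservatism to missing sirolimus scores. Section 9.3 requires a protocol amendment for a change to the primary analysis; it should be made before outcome data are seen.

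Simply leaving control scores missing would also remove the excess, but it drops randomised children from a test that 9.4 says will evaluate everyone, and it discards their 1-year scores.

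Costs: about 2-3 points of power (about 69% to 67% at difference 15, SD 20, three missing per arm); a test that runs below 5% when sirolimus scores are missing; and recalculation of the Table 8 columns that take missing values into account.
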